## Abstract

**Background:**

Home-based cardiac rehabilitation is a promising approach to improve access and adherence to cardiac rehabilitation (CR), which remains underutilized. However, monitoring patient adherence and safety during home-based exercise is challenging. Therefore, we develop and implement a home-based exercise cardiac telerehabilitation (HBECTR) program, integrating structured exercise guidance with remote monitoring.

**Objective:**

This trial is designed as a pilot feasibility study to evaluate the practicality, safety, and preliminary effects of HBECTR in patients who have undergone percutaneous coronary intervention (PCI). The primary objective is to analyze the effect of HBECTR on patients’ adherence to CR, while the secondary objective is to measure the effect of HBECTR on the functional capacity of patients after PCI.

**Methods:**

This study is a quasi-experimental nonequivalent control group pretest-posttest. The eligible participants are adults (≥18 y), patients with coronary artery disease after successful PCI, and patients having active health insurance. Patients will be consecutively recruited from [name] Hospital, Yogyakarta, Indonesia, with a minimum of 60 patients after PCI as samples, divided into 2 groups: an intervention group and a comparison or control group. The intervention group will receive hybrid cardiac rehabilitation. Patients will be scheduled to do exercise twice a week at the hospital and 3 times a week at their home. When patients exercise at home, they will have to wear the smartwatch “CovWatch,” which will be connected to the web-based app (App Rehab Cardio) to monitor their vital signs and the distance of walking. The control group will get usual care (center-based cardiac rehabilitation). The data will be analyzed using the Student *t* test to see if the data comply with the normality assumption. This protocol received approval from the institutional review board of the Faculty of Medicine, Public Health, and Nursing UGM (approval number: KE/FK/0850/EC/2024).

**Results:**

The recruitment of the patients started in August 2024. This study is being funded since February 2025. During the submission, we have recruited 63 patients in both intervention and control groups. The intervention for both groups was finished in June 2025, and the data are being analyzed.

**Conclusions:**

It is expected that the HBECTR program will be feasible and safely implemented in low- and middle-income countries, particularly in Indonesia. By integrating a telerehabilitation model, it is expected that HBECTR will improve patients’ adherence to CR and also increase the functional capacity of patients after PCI.

## Introduction

### Background

Cardiovascular disease (CVD) is the leading cause of death and disability worldwide, with the highest death rates (more than 75%) occurring in low- and middle-income countries [1]. Indonesia reported 765,660 deaths from CVD in 2021, placing Indonesia in the top 20% rank of countries with the highest mortality based on age-standardized mortality from CVD. Furthermore, Indonesia has relatively high rates of non-high-density lipoprotein cholesterol in women and tobacco use in men when compared to other countries globally. Indonesia has implemented 4 of 8 key CVD-related policies. It does have a national action plan for CVDs in place and an operational unit within the Ministry of Health with the responsibility for managing non-communicable diseases; however, the action plan to reduce physical inactivity has not been developed [2].

Cardiac rehabilitation (CR), a multicomplex intervention that is a class 1A recommendation from the American Heart Association and the American College of Cardiology, aims to improve the health condition of patients [3,4], reduce mortality, enhance recovery, and support positive behavioral changes to reduce risk factors [4-7]. Although the effectiveness and benefits of the CR program have been proved, it is still underutilized, and its access is limited [5]. Globally, the level of participation and compliance of patients undergoing CR is still low [8], especially in countries with limited resources [9]. The compliance rate for patients with post-heart attack is 14%‐35% [10] and around 24% for patients with coronary heart disease with various conditions [11]. It means that more than 80% of the patients who are referred to CR do not participate in the program [12]. Patients’ participation and adherence to CR are essential to determine the success of prevention efforts and improve patients’ condition [13].

Exercise-based cardiac rehabilitation (EBCR) is essential for patients undergoing revascularization (postpercutaneous coronary intervention [PCI]) because they often experience decreased exercise capacity and physical activity levels, and both of these indicators are very important for predicting postprocedure morbidity and mortality [14]. Furthermore, these patients also need self-management to improve their health conditions and other clinical outcomes, such as reducing depression and anxiety, mortality, and morbidity and improving their quality of life [15]. EBCR focuses on improving cardiac endurance, exercise capacity, muscle strength, physical activity levels, and quality of life through health education and lifestyle modification [14]. Physical exercise is the main pillar (core stone) of cardiac rehabilitation [13] because it can increase functional capacity and encourage patients to develop and maintain an active lifestyle that can reduce the risk of recurrence in the future [16].

In Indonesia, CR is predominantly implemented in hospital-based or center-based cardiac rehabilitation (CBCR) settings, as the national health insurance scheme—Badan Penyelenggara Jaminan Sosial (BPJS)—currently reimburses only CBCR services. In contrast, home-based cardiac rehabilitation (HBCR), cardiac telerehabilitation, and virtual rehabilitation programs are not yet covered by the insurance system [17]. Although BPJS facilitates access to CBCR, CR services remain limited because not all hospitals in Indonesia have established CR facilities. Similar to other countries in the Southeast Asia region, most available programs are concentrated in tertiary care centers or major urban areas [18]. [name] Hospital in Yogyakarta is one of the few hospitals in Indonesia that provides CR services and has offered EBCR since 2006. However, the accessibility and continuity of CR remain major challenges, particularly for patients who live far from the hospitals or face transportation and time constraints.

The implementation of EBCR at [name] also has evolved considerably between the pre- and post-COVID-19 periods, particularly in terms of session frequency and delivery format. Before the pandemic, the EBCR program consisted of 10‐12 sessions, typically conducted 3‐5 times per week. During the pandemic, however, the frequency was reduced to twice per week while maintaining the total number of 10‐12 sessions [17]. At present, most patients participate in CBCR twice weekly for 4 weeks, resulting in approximately 8 sessions overall. The duration and frequency may be extended depending on each patient’s clinical condition or physician’s recommendation. Nevertheless, the current practice remains below the national guideline, which recommends that patients engage in exercise 4‐7 times per week to achieve optimal outcomes [19]. Therefore, incorporating home-based exercise as part of a hybrid or fully HBCR program may serve as a feasible and scalable alternative to meet the recommended exercise frequency, enabling patients to continue rehabilitation safely and effectively at home on nonhospital days.

HBCR has a positive effect on patient self-efficacy [7], which will encourage patients to behave positively. Besides, home-based exercises have been proven to be very effective in improving patient conditions because they can empower patients to monitor the exercises they do independently [13]. Moreover, HBCR has the same safety and effectiveness as hospital or CBCR in improving patient functional capacity and various other clinical outcomes [1,5,20-22]. HBCR has emerged as a promising alternative to CBCR [5,23].

Despite the various advantages and benefits of HBCR, there are several obstacles, such as the absence of clear guidelines regarding dosage and components, its limited implementation in certain cases, and its limited implementation in all countries. The research and implementation of HBCR are mostly in developed countries such as the United States, Australia, and England [5,24].

Adding artificial intelligence that can interpret data and monitor the implementation of CR can increase the safety and feasibility of HBCR. Devices installed or worn by patients are expected to identify the patients’ toleration of exercise dose and monitor the vital signs to ensure patient safety during exercise at home [20]. The use of information technology in its implementation is predicted to increase the long-term effects of HBCR [24]. Smartphones or mobile devices (20/31, 65%), web-based portals (18/31, 58%), and email or SMS (11/31, 35%) are the most often used information technologies to support CR [12]. In this study, we will use a web-based app (dashboard) to support the implementation of home-based exercise cardiac telerehabilitation (HBECTR).

Although several studies support the implementation of telerehabilitation, there are still no definitive data on the efficacy of HBECTR compared to CBCR, thus requiring further research [23,25]. Besides, the biggest challenge today is how to improve patient adherence and compliance in CR, the development of HBCR guidelines, and the implementation of information technology in HBCR that can be applied in countries with limited resources, like Indonesia. Therefore, this study is designed as a pilot feasibility trial to evaluate the practicality, safety, and short-term effects of a digitally supported HBECTR program in Indonesian patients after PCI. This is the first pilot study in Indonesia implementing digitally supported HBCR, particularly using a web-based platform, and addressing a critical gap in low- and middle-income country settings where CR utilization remains low. The pilot nature of this study allows us to examine the feasibility of the program, adherence, safety monitoring, and digital health implementation in a resource-limited setting.

### Objectives

This study aimed to evaluate the effectiveness of an HBECTR program for patients after PCI. The primary objective was to assess the effect of HBECTR on adherence to CR, while the secondary objective was to determine its effect on patients’ functional capacity.

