### Hypotheses

In this study, we examined two hypotheses:

There is no difference in functional capacity between the HBECTR group and the control group (CG; H_0_) or HBECTR will improve functional capacity compared to the control (H_1_).There is no difference in adherence between the HBECTR group and the CG (H_0_) or HBECTR will improve adherence to CR compared to the control (H_1_).

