### Study Procedures

To assess the efficacy of the HBECTR program, we divided subjects into 2 groups: the intervention group and the control group (Table 1). The CG will receive standard hospital CR or CBCR, while the treatment group will receive HBECTR. We define HBECTR as exercise-based cardiac rehabilitation conducted in a hybrid setting, both in the hospital and at the patient’s home, supported by a telemonitoring system.

We will use a telemonitoring system consisting of a smartwatch (CovWatch) produced by PT CovWatch Karya Nusantara, Indonesia, connected via the internet to the web-based app (dashboard), namely “Telerehabilitasi Kardiovaskular (TEKAD)” (App Rehab Cardio) [36]. We developed and conducted usability testing before the dashboard was released (will be reported separately). Prior to the initiation of the study, an accuracy test will be conducted on 10‐20 patients as part of the CovWatch protocol. A standardized calibration check will be performed at baseline by comparing CovWatch-derived heart rate (HR) with a clinical pulse oximeter at rest and during walking test. Data validity will be monitored through automated system flags for missing data, connectivity loss, and out-of-range physiological values. Mitigation strategies will include repeating measurements, instructing participants on proper device placement (detailed in the guidance book for patient), verifying battery status, and resynchronizing data in case of delayed transmission. All sensor data will be stored with time stamps to identify anomalies and enable manual quality checks.

Before starting the exercise, all patients will undergo a pretest to measure functional capacity using the 6-minute walk test (6MWT) [37]. This pretest is carried out when the patient is still hospitalized or during the first check-up after PCI, according to hospital policy. The cardiologist will prescribe an exercise regime tailored by patients based on this baseline 6MWT, in accordance with the CR guidelines in Indonesia [19]. After the patients have finished all CR programs, they will do the 6MWT for a posttest. The 6MWT for both pretest and posttest will be done at the CR center, [name] Hospital, Yogyakarta. The intervention of this study will be reported according to the TIDieR (Template for Intervention Description and Replication) [38], in conjunction with the CERT (Consensus on Exercise Reporting Template) [39] and mERA (mHealth Evidence Reporting and Assessment; Checklist1^4^).

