### Statistical Analysis Planning

All data will be analyzed using the IBM SPSS software (version 29). We will use MI for missing data. MI is a widely used technique for handling missing data in various fields, including medical, social, and ecological research.

Data analysis will be performed primarily on participants who complete both baseline and postintervention assessments, regardless of their adherence level during the intervention period (*completer analysis*). Participants who withdraw or are lost to follow-up before the posttest will be excluded from outcome analysis but will be included in the descriptive analysis of recruitment, adherence, and retention rates. This approach is considered appropriate for pilot quasi-experimental studies, where the primary aim is to assess feasibility, acceptability, and signal of effect rather than to test definitive efficacy [31,35].

To minimize potential bias due to nonrandom assignment, baseline characteristics between the groups will be compared using 2-tailed independent *t* tests or chi-square tests. In addition, propensity score adjustment will be applied in exploratory models to control for potential confounding variables (eg, age, sex, baseline functional capacity, comorbidity), following recommendations for quasi-experimental design analysis [33].

All statistical analyses and reporting will follow the principles outlined in the CONSORT-EHEALTH 2011 (Consolidated Standards of Reporting Trials of Electronic and Mobile Health Applications and Online Telehealth) [47] (Checklist 3). Descriptive statistics will summarize feasibility outcomes (recruitment, adherence, completion rates, safety events), while inferential tests (2-tailed paired *t* tests or analysis of covariance) will be used to explore within- and between-group changes (including means and SDs) in functional capacity and adherence measures. Statistical significance will be interpreted cautiously, given the pilot nature and limited sample size of the study [31,35].

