Furthermore, several potential limitations should be acknowledged in this quasi-experimental study. First, the intervention may yield null or minimal effects, particularly on adherence to cardiac rehabilitation and functional capacity, due to variability in participant engagement, baseline fitness levels, or external barriers such as comorbidities or limited motivation. Second, feasibility challenges are anticipated, including variable access to technology, differences in digital literacy, difficulties in remotely monitoring safety, and potential missing data from nonadherence or technical issues. Using a wearable device (smartwatch) is preferable to most patients; however, it has challenges in its implementation and needs further exploration to gain a deeper understanding of patients’ needs and preferences [52]. Finally, resource limitations may constrain implementation, including limited personnel for supervision, insufficient devices for remote monitoring, costs associated with web-based platforms, and the need for staff training and scheduling coordination.

In addition, this study also has limitations, including its modest sample size, and the short follow-up duration limits its generalizability to the broader population. These are intentional features of a pilot feasibility trial that focuses on testing feasibility, safety, and preliminary efficacy signals rather than providing conclusive evidence of effectiveness [32]. Clinical trials of physical activity and rehabilitation interventions are challenging; therefore, researchers can use pilot and feasibility studies to enhance the rigor of future trials [35].

Despite these challenges, the study provides valuable insights into the practicality and potential impact of HBECTR, informing the design of larger, fully powered trials. Future research is needed to enhance the study in multicenters with multiple outcomes. Longer-term effects, sustainability, and cost-effectiveness should be evaluated in a subsequent definitive trial.

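### The aim, hypotheses and significance rule set up an effectiveness verdict that the protocol elsewhere says this nonrandomised pilot is not meant to give

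*Protocol article*

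**What the plan says.** Two sets of statements stand in the current text of the protocol article.

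**Toward an effectiveness verdict**
- Objectives: "This study aimed to evaluate the effectiveness of an HBECTR program for patients after PCI", followed by "The primary objective was to assess the effect of HBECTR on adherence to CR".
- Hypotheses: two null and alternative pairs, with alternatives "HBECTR will improve adherence to CR compared to the control" and "HBECTR will improve functional capacity compared to the control".
- Study Procedures opens its account of the two groups with "To assess the efficacy of the HBECTR program".
- Statistical Analysis Planning (closing paragraph): P<.05 counts as significant in all tests, with no multiplicity adjustment.

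**Toward a pilot that gives no such verdict**
- Abstract, Objective, and again Study Design: "This trial is designed as a pilot feasibility study to evaluate the practicality, safety, and preliminary effects of HBECTR".
- Statistical Analysis Planning defends its completer analysis as suited to pilot quasi-experimental studies, "where the primary aim is to assess feasibility, acceptability, and signal of effect rather than to test definitive efficacy". It adds that the inferential tests explore changes and that significance will be read cautiously.
- Discussion: the small sample and short follow-up are deliberate features of a pilot that looks for feasibility, safety and early signals "rather than providing conclusive evidence of effectiveness".
- Samples: the intervention group was recruited and followed up before the control group started, and the authors accept that adjustment cannot fully remove the resulting time-related bias.

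**The concern.** An effectiveness aim, paired hypotheses of improvement and a fixed significance level together make an instruction: test, then conclude. The design described in the same article cannot carry that conclusion. Groups are not randomised, they are enrolled one after the other, and the outcome analysis leaves out patients lost before the posttest. The pilot label is used to justify that lighter analysis, and the same analysis is then available to decide the effect hypotheses.

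The article thus leaves two readings open. A significant difference could be reported as effectiveness under Objectives. A nonsignificant one could be reported as no difference under Hypotheses, or set aside as a mere pilot result under the Discussion. The intervention had finished and analysis was under way at submission, so the reading should be settled in the document and not once the results are known.

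The comparison also answers only part of what a pilot needs. Adherence is sessions attended over sessions prescribed: 8 + 12 = 20 sessions in the intervention group and 8 in the control group. A difference between those percentages does not by itself show whether patients can carry out the 20-session hybrid programme. The intervention group's own completion does.

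**Working it through.** The point rests on the text; the arithmetic only shows its scale.

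**1. The statements compared**

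| Element | Effectiveness reading | Pilot reading |
|---|---|---|
| Aim | Objectives: effectiveness; Study Procedures: efficacy | Abstract and Study Design: practicality, safety, preliminary effects |
| Hypotheses | Improvement over control, for adherence and for functional capacity | None needed for a signal of effect |
| Decision rule | P<.05 in all tests | Tests explore; significance read cautiously |
| Permitted conclusion | Accept or reject the null | Discussion: no conclusive evidence of effectiveness |

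The primary outcome does not differ between the columns. It is adherence in the Abstract, Objectives, Study Design, Measurement and Statistical Analysis Planning. The conflict lies in the aim, the decision rule and the permitted conclusion.

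**2. The plan's own sample size**

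Samples gives 30 per group from a 30 m walk difference, 80% power, 5% type I error and 10% dropout. The article does not print the SD, so the figure can only be solved backwards. With n = 2(1.96 + 0.842)² SD² / 30² and an assumed two-sided SD of 39 m, n = 2 × 7.849 × 1521 / 900 = 26.5, rounded up to 27, and 27 / 0.9 = 30. This calculation concerns walk distance, the secondary outcome. The same paragraph also justifies 30 per group by a rule for pilot sizes. The printed basis therefore says nothing about power for adherence.

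**3. Illustration for adherence**

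Assumptions, none stated in the article for this comparison: 27 to 30 analysed per group (30 with and without 10% loss), adherence dichotomised at the 80% definition in Measurement, and a two-sided pooled z test at 5%. Power is found by enumerating all outcomes.

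| Assumed proportions adherent | n = 27 per group | n = 30 per group |
|---|---|---|
| 80% v 60% | 0.377 | 0.392 |
| 80% v 45% | 0.775 | 0.816 |

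The 95% half-width of the difference is 1.96 × √[(p₁(1−p₁) + p₂(1−p₂)) / n]:
- 80% v 80%, n = 30: 1.96 × √(0.32/30) = 0.202; n = 27: 0.213.
- 80% v 60%, n = 30: 1.96 × √(0.40/30) = 0.226; n = 27: 1.96 × √(0.40/27) = 0.239.

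The range is about ±20 to 24 points.

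The plan also expresses adherence as a percentage and names t tests, ANCOVA or nonparametric tests, so these figures are not the power of the planned analysis.

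**4. What the intervention group alone can show**

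Exact (Clopper-Pearson) 95% CIs: 24/30 = 80% gives 61.4-92.3%; 27/30 = 90% gives 73.5-97.9%. The counts are examples.

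**The case against.** The strongest reply is that a between-group comparison belongs to this pilot's stated purpose. The Abstract and Study Design include preliminary effects, the statistics section includes a signal of effect, and the Discussion speaks of early efficacy signals. This stands: comparing the groups is not the fault, and an estimate with its interval fits the pilot label. An effectiveness aim decided at P<.05 does not.

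Second, the statistics section says that tests explore and that significance is read cautiously. That is a real mitigation, and it means the article does not plainly order an effectiveness headline. But it governs tone, while Objectives, Hypotheses and the blanket P<.05 rule are left unqualified.

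Third, feasibility is analysed. Recruitment, adherence, completion and safety events are summarised, and RE-AIM reporting and interviews are planned. A reader might infer that the study has two competing primary outcomes, or that feasibility is ignored; the article supports neither.

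A reader might also fault a directional alternative beside two-tailed tests. Testing a directional expectation two-sided is ordinary practice, and the article gives no sidedness for the between-group Student t test, so nothing rests on this.

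Finally, swapping the primary objective after data collection would itself be open to criticism. That also stands, and the fix avoids it.

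**Conclusion.** The inconsistency is real and should be corrected. Objectives, Study Procedures, Hypotheses and the P<.05 rule point to a verdict on effectiveness that the statistics section and the Discussion say this sequentially enrolled, nonrandomised pilot is not meant to deliver. The cautionary wording reduces the problem without resolving it.

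The textual finding depends on no numerical assumption. Its practical size can only be illustrated: under the assumed proportions for dichotomised adherence, a 20-point difference would be detected about 38-39% of the time, and roughly 80% power needs a gap of about 35 points (80% v 45%). Other proportions, or analysis of the percentage itself, would give other figures. Greater precision would not remove the bias from sequential enrolment that the authors already concede.

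It would be tempting to conclude that feasibility must replace adherence as the primary question, or that the 80% cut-off is a test of feasibility. Neither follows. Adherence is named primary consistently, and 80% defines when an individual patient is adherent; it is not a criterion for the study.

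**What to change.** 1. Keep adherence as the primary outcome.
2. In Objectives and Study Procedures, replace the effectiveness and efficacy wording with preliminary effects, to match the Abstract, Study Design and Discussion.
3. Label the two hypothesis pairs exploratory.
4. Report the between-group contrasts in adherence and 6-minute walk distance as estimates with 95% CIs, with no accept or reject conclusion on effectiveness. Limit the P<.05 sentence accordingly.
5. Beside them, report for the intervention group: session completion, hospital and home separately; the proportion of patients reaching the 80% definition; and retention to posttest. Give each a 95% CI, exact where it is a proportion of patients. If session completion is shown as a mean percentage, the patient must be the unit for its interval, because sessions within a patient are not independent.
6. Do not read 80% as a study-level feasibility threshold.
7. Date the change and state that it was made after data collection: the intervention ended in June 2025 and analysis was under way at submission.

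The cost is wording and a few table rows from data already collected. The sponsor gives up a significance-based claim of effectiveness, which the Discussion already disclaims.
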